### **8.2. Univariate analysis**

The Statistical Package for the Social Sciences (SPSS) will be used to perform univariate analyses. ANOVA will be performed to determine possible differences in gut flora, fat absorption, REE, activity and body composition between the four groups, with time (baseline, 6 weeks, 12 weeks) as the within-subject factor and group (normal weight-GT, normal weight-control, obese-GT, obese-control) as the between-subject factor. Post hoc, a Scheffe's *F* test will be applied. Statistical significance will be set at  $p < .05$ .

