## 2. OBJECTIVES

The objective of this study is to investigate the long-term effects of green tea on gut flora, fat absorption, resting energy expenditure and body composition. The primary aim of the present study is to examine whether green tea supplements affect fat metabolism, gut flora and body weight.

This primary objective implies that green tea increases faecal fat and decreases fat absorption, resulting in decrease in digestible energy of the diet. Green tea may inhibit lipase activity. Inhibition of digestive lipase activity could significantly affect dietary lipid absorption and could increase lipid excretion into the faeces. Faecal fat excretion will be measured to determine the lipid absorption (10).

Previous studies have shown comparable effects in animal studies (4-6). This study needs to determine whether green tea also increases faecal fat and lowers the fat absorption in humans and will test the hypothesis that the increase in faecal fat will be larger in the green tea conditions compared to the conditions without green tea.

Furthermore we will investigate whether green tea has positive effects on gut flora and will increase the relative proportion of *Bacteroidetes* to *Firmicutes* and that this change in *Firmicutes/Bacteroidetes* ratio will be larger in obese subjects compared to normal weight subjects. Metabolism of polyphenols by microbiota involves the cleavage of glycosidic linkages. Glycans, which are the product of glycosidic cleavage, are necessary for survival of the intestinal microbiota as a nutrient foundation. *Firmicutes* possess a disproportionately smaller number of glycan-degrading enzymes than *Bacteroidetes*. Furthermore, *Firmicutes* are more repressed than the *Bacteroidetes* by phenolic compounds' antimicrobial properties. The *Bacteroidetes* community prevails following dietary polyphenol intake and its fermentation to phenolic compounds, due to having more glycan-degrading enzymes, so this may thus be a mechanism by which dietary polyphenols exert their weight lowering effect (9).

Finally, we will investigate whether a supplementation with green tea polyphenols is proposed for weight loss via an increase in the resting energy expenditure and fat oxidation.

Four groups consisting of control groups and green tea groups with normal weight subjects and obese subjects will be applied in order to completely answer the research questions:

- Normal weight without green tea (NW/control)

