#### 4.4. Sample size calculation

The primary endpoint of this study is the change in gut flora and fat absorption.

For the sample size calculation the following formula was used:

$$N = 2 + (Z_{1-\beta} + Z_{1-\alpha/2})^2 \times \sigma^2 / (\mu_{GT} - \mu_{CONTROL})^2$$

Subject population size was calculated using G\*Power 3.1.2 where  $\alpha$  was 0.05,  $\beta$  was 0.95 using group mean body weight changes from past papers (12) to calculate the effect size, the population was finalized as 45 per group and an additional 5 (drop-out of 10%) will be included in the population size for any unforeseeable circumstances which may lead to subjects dropping out.

The calculated sample size will be:

|                    |           |           |
|--------------------|-----------|-----------|
| Means:             | u1 = 72.5 | u2 = 71.4 |
| Standard deviation | SD1= 1.4  | SD2= 1.7  |

Confidence interval is  $\alpha=0.05$ , for  $\beta=0.95$

$$N1 = N2 = 2 + (Z(1-\beta) + Z(1-\alpha/2))^2 \times \frac{(\sigma_1^2 + \sigma_2^2)}{(\mu_1 - \mu_2)^2}$$

45 people per condition (two conditions; green tea and placebo).

Taking a drop-out of 10% into account, 50 subjects will be included per condition and herewith 100 subjects will be included in the experiment.

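### Section 4.4 sizes a pooled green tea versus placebo comparison, but Section 8.2 tests a four-level group factor with Scheffé and names neither contrast that Section 2 asks about

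*Protocol*

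**What the plan says.** Section 2 of the protocol poses two comparative questions. The first is a treatment question on faecal fat: whether the "increase in faecal fat will be larger in the green tea conditions compared to the conditions without green tea". The second asks whether the change in the Firmicutes/Bacteroidetes "ratio will be larger in obese subjects compared to normal weight subjects", which is a treatment-by-BMI-class question.

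Section 4.4 sizes the first kind of question only, and on body weight. It reports "45 people per condition (two conditions; green tea and placebo"), and then adds for losses: "Taking a drop-out of 10% into account, 50 subjects will be included per condition".

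Section 8.2 plans an ANOVA with "time (baseline, 6 weeks, 12 weeks) as the within-subject factor and group (normal weight-GT, normal weight-control, obese-GT, obese-control) as the between-subject factor". A Scheffé test follows, with no contrast named, at a significance level of 0.05.

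**The concern.** The design is a two-by-two layout: randomised treatment within two BMI classes. Section 8.2 flattens it into one factor with four levels. An omnibus test on that factor asks whether the four groups differ in any way at all. It isolates neither the treatment effect, for which the sample was chosen, nor the difference in treatment effect between obese and normal-weight subjects.

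The follow-up adds a cost. Scheffé protects every conceivable contrast among the four groups, whereas Section 2 needs two that can be written down in advance. The critical value rises accordingly, and power for the sized comparison falls. At stake are the match between the stated power and the test that will be run, and whether a significant result would answer the questions in Section 2.

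**Working it through.** **Inputs (Section 4.4).** Means "u1 = 72.5 | u2 = 71.4", a difference of 1.1; SDs 1.4 and 1.7; alpha 0.05; 45 per condition. The 0.95 is printed as beta and is read here as power. Three assumptions are mine:
- The SDs are SDs of change. The section says that it used weight changes, but the printed means look like body weights.
- The 90 evaluable subjects split equally, 90/4 = 22.5 per group.
- Unless stated otherwise, the treatment effect is the same in both BMI classes.

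**Effect size.** Pooled SD = √[(1.4² + 1.7²)/2] = √2.425 = 1.557; d = 1.1/1.557 = 0.706.

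**The plan's own figure.** N = 2 + (z_power + z_alpha)² × (1.96 + 2.89)/1.1².
- One-sided 0.05, power 95%: 43.38 + 2 = 45.4. Exact t gives 45.
- Two-sided 0.05 as the formula is printed, power 95%: 52.09 + 2 = 54.1. Exact t gives 54.

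So 45 reproduces at 95% power only with a one-sided test. With 45 per condition, a two-sided test has about 91%. This gap lies in Section 4.4 and is separate from the choice made in 8.2.

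**Pooled treatment contrast at 45 versus 45.** Noncentrality = 0.706 × √(45/2) = 3.35, with 90 − 4 = 86 error df.
- Planned 1-df contrast, two-sided: critical t = 1.988, power 91.2%.
- Scheffé: critical value √[3 × F(0.95; 3, 86)] = 2.852, power 69.0%.

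**Omnibus four-group F on change scores (3 and 86 df).** Noncentrality = n × Σ(mean − grand mean)²/SD².
- Equal effect in both classes: 22.5 × 4 × 0.55²/2.425 = 11.23, power 79.3%.
- Effect in one class only: 22.5 × 0.75 × 1.1²/2.425 = 8.42, power 65.7%.

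**Group-by-time F (6 and 172 df).** Compound symmetry is assumed, so the within-subject variance is 2.425/2 = 1.2125.

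| Time course of the effect | Both classes | One class only |
|---|---|---|
| Linear to week 12 | 68.5% | 53.8% |
| Complete by week 6, or at week 12 only | 82.6% | 68.5% |

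**If nobody drops out (25 per group).** Scheffé pooled contrast 75.2%; planned contrast 93.8%; omnibus on change 83.9% (both classes) or 71.0% (one class).

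**What cannot be computed.** The protocol gives no mean difference or SD for the Firmicutes/Bacteroidetes ratio or for faecal fat, so no power can be given for either.

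**The case against.** - **Sizing on two pooled conditions is legitimate.** It is the right basis for a treatment main effect in a two-by-two design. The four-level factor has the same cell means and the same error term as treatment by BMI class. This stands: splitting the sample by BMI class does not itself cost the power. The loss comes from the omnibus test and Scheffé in place of named contrasts.
- **Contrasts can be left to an analysis plan.** This is true in general, and such a plan may exist. But Section 8.2 is not silent: it fixes the factor and the follow-up procedure, and those choices do not fit Sections 2 and 4.4.
- **A reader might infer that the trial's real power is 32-69%.** The documents do not support that. The range covers Scheffé contrasts only, and the omnibus test reaches about 79% on change scores and up to 83% for group by time. The 32% belongs to green tea versus control within one BMI class, which is neither of the two Section 2 questions set out above; an unadjusted contrast there has only 65%.
- **A reader might infer that the obese-versus-lean hypothesis can never be tested.** Scheffé would permit that contrast; the protocol simply does not name it. An interaction power of 38% planned or 13% by Scheffé can be calculated by placing the whole 1.1 in one class, but that uses body-weight inputs for a hypothesis about gut flora.
- **A reader might infer that treatment is confounded with BMI class.** A group main effect can indeed be significant only because lean and obese subjects differ, and Section 1 says that their microbiota do. A constant baseline difference drops out of group by time, however, so the objection does not reach that test.

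**Conclusion.** The point holds in this form: the analysis fixed in Section 8.2 does not match the comparison sized in Section 4.4 or the two questions in Section 2. For the comparison that was sized, the like-for-like loss is from 91% with a planned two-sided contrast to 69% under Scheffé. The omnibus test lies at about 66-79% on change scores and 54-83% for group by time, and a significant result would not show which group changed. Every one of these figures is below the stated 95%.

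The figures apply to body weight alone. They rest on reading 1.4 and 1.7 as SDs of change, on an equal four-way split of 90 evaluable subjects and, for group by time, on compound symmetry. Correcting Section 8.2 brings the power to about 91%, not 95%. The remaining shortfall comes from the one-sided/two-sided discrepancy in Section 4.4, and two-sided 95% would need 54 evaluable subjects per condition.

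**What to change.** **Section 8.2.** Replace the four-level group factor with treatment (green tea or placebo), BMI class and time, with their interactions. Name the 12-week treatment contrast on the change, pooled over BMI class, as the primary test. Name the treatment-by-BMI-class contrast on the change as the test of the obese-versus-lean hypothesis. Keep Scheffé for unplanned comparisons only.

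**Section 4.4.** Restate the power of the pooled two-sided contrast at 45 per condition as about 91% for body weight, and state that the trial is not sized for the interaction.

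**Optional refinement.** Section 2 words the gut-flora hypothesis in both orientations of the ratio, while Section 6.1.1 fixes Firmicutes/Bacteroidetes. Analysing log(Firmicutes/Bacteroidetes) would give the same test either way round.

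**Cost.** Wording in two sections, with the same subjects, visits and data. The downside is that unplanned pairwise comparisons become exploratory.

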## **9. ETHICAL CONSIDERATIONS**

### **9.1. Regulation statement**

The study will be conducted according to the principles of the Declaration of Helsinki (9th version, October 2008, Seoul) and in accordance with the Dutch version of the Medical Research Involving Human Subjects Act (in Dutch: Wet Medisch-wetenschappelijk Onderzoek met mensen; WMO).

### **9.2. Recruitment and consent**

Subjects from the student population will be recruited by advertisements in local newspapers and on notice boards at the Maastricht University. They will be informed about the study by reading the provided written 'subject information'. The researchers will orally check their comprehensiveness. An independent person who's well informed about the study could eventually provide additional information, and subjects will be referred to the 'Centrale Commissie Mensgebonden Onderzoek' (CCMO)-brochure 'General information for research participants' that contains general information about medical-scientific research. After being well-informed subjects will get one week before they have to decide to participate in the study. All subjects will confirm their approval for participation by signing an informed consent (IC) form.

### **9.3. Benefits and risks assessment, group relatedness**

This study does not have any benefits for the subjects themselves, but will give possible new knowledge for treatment of obesity. Besides, the study does not include any major risk for the subjects. The collection of faeces will be harmless. Anthropometric and body composition measurements, performed within several minutes during the screening, will not be invasive for the subjects. Deuterium dilution has been shown to be a safe method for determining total body water. Subjects have to consume an amount of about 150 mL of water in which a small amount of deuterium is diluted. The taste of the solution is comparable to normal water (21). Furthermore, the registration of oxygen consumption and carbon dioxide production with the ventilated hood will be performed during an unconscious process. The air in the hood is continuously regulated. Administering green tea will not form any health risk. Green tea is a natural product, which is safe in the given dose that will not exceed the maximum recommended daily dose.

The completion of screening questionnaires will take about 30 minutes.

Accidental findings during the screening related to health status will be communicated to the concerned subjects, whereafter they can individually undertake further steps.

Green tea and placebo capsules will be processed, handled, packaged and transported by Taiyo Kagaku Co., Ltd., as described in the certificate of analysis. After arrival at the University the product will be stored in a locked food depot in the research kitchen. Green tea and placebo capsules will be stored for a maximum period of one year, which corresponds to the maximum duration of the study and will not exceed the expiration date of the product. A certified dietician controls the storage of the products.

Further information can be found in the guideline 'MEC azM/UM for preparation, delivery and administration of products for human usage in clinical studies'.

#### **9.4. Compensation for injury**

The investigator has a liability insurance, which is in accordance with article 7, subsection 6 of the WMO.

The sponsor also has an insurance which, is in accordance with the legal requirements in the Netherlands (Article 7 WMO and the Measure regarding Compulsory Insurance for Clinical Research in Humans of 23th June 2003). This insurance provides cover for damage to research subjects through injury or death caused by the study.

€ 450.000,-- (i.e. four hundred and fifty thousand Euro) for death or injury for each subject who participates in the Research;

€ 3.500.000,-- (i.e. three million five hundred thousand Euro) for death or injury for all subjects who participate in the Research;

€ 5.000.000,-- (i.e. five million Euro) for the total damage incurred by the organisation for all damage disclosed by scientific research for the Sponsor as 'verrichter' in the meaning of said Act in each year of insurance coverage.

The insurance applies to the damage that becomes apparent during the study or within 4 years after the end of the study.

#### **9.5. Incentives**

After completion of the study subjects will receive a financial compensation of 100 euro.

Possible travel expenses will be declared.

## **10. ADMINISTRATIVE ASPECTS AND PUBLICATION**

### **10.1. Handling and storage of data and documents**

Subjects' personal information will be confidentially handled during the study, according to the Dutch Personal Data Protection Act (Wet bescherming persoonsgegevens; Wbp). Results will be linked to the intervention and not to individual subjects. Subject numbers (e.g. number 1) in combination with treatment codes (NW/control, Ob/control, NW/GT, Ob/GT) will be used throughout the study. Only the researcher is familiar with subject information, so privacy of personal information is guaranteed. If desirable, subjects will be informed about their personal study results at the end of the study. Collected body material (urine and faeces) will be destroyed after publication of the results, body material will be kept for a maximum period of 15 years. Personal data will be kept for a period of 15 year, which is the legal time to keep medical data. Hereafter the data will be destroyed.

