- Obese without green tea (Ob/control)
- Normal weight with green tea (NW/GT)
- Obese with green tea (Ob/GT)

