### 3. STUDY DESIGN

#### 3.1. Study design

The study will be conducted in randomized, placebo-controlled, double-blind parallel design with four randomly sequenced experimental conditions.

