### 6.2. Randomisation, blinding and treatment allocation

The study will be conducted in a randomized, placebo-controlled, double-blind parallel design with four randomly sequenced experimental conditions. Randomisation will take place using a computerized randomization program ('Randomizer' macro in Excel).

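### Section 10.1 pairs every subject number with an open treatment code throughout the study, which contradicts the double-blind design

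*Protocol*

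**What the plan says.** On blinding, section 6.2 states: "The study will be conducted in a randomized, placebo-controlled, double-blind parallel design with four randomly sequenced experimental conditions". Section 3.1 says the same in almost identical words, and the Summary also calls the trial double-blind. On allocation, section 6.2 adds only this: "Randomisation will take place using a computerized randomization program ('Randomizer' macro in Excel". It does not say who runs the macro or who keeps the resulting list.

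On identifiers, section 10.1 states: "Subject numbers (e.g. number 1) in combination with treatment codes (NW/control, Ob/control, NW/GT, Ob/GT) will be used throughout the study".

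The codes are explained in section 2, in the list of the four groups. Two of the entries read "Normal weight without green tea (NW/control" and "Normal weight with green tea (NW/GT"; the two obese groups follow the same pattern.

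The only access restriction in section 10.1 is this: "Only the researcher is familiar with subject information, so privacy of personal information is guaranteed".

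**The concern.** A blinded trial needs an identifier that does not reveal the arm while data are being collected. The identifier in section 10.1 does reveal it. The first half of each code (NW or Ob) is harmless, because BMI class is a visible baseline trait. The second half (GT or control) is the randomised treatment itself.

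What is at stake is whether the staff who run the visits are blind. Several procedures leave them room to influence the result without intending to:

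- waist and hip are measured by tape (section 6.3.1);
- the resting energy measurement depends on how the rest period and the test are conducted (section 6.3.3);
- subjects are instructed on diet, activity and the three-day faecal collection (sections 3.2, 6.3.4, 6.3.6 and 6.3.7);
- the investigator may withdraw a subject for urgent medical reasons, and withdrawn subjects are replaced (sections 6.4 and 6.5).

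The placebo capsules in section 5.1 are there to conceal the treatment. An open code on working records would undo that for the staff who use those records.

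**Working it through.** No arithmetic applies. The check sets the relevant sections side by side.

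1. **Design claim.** The Summary, section 3.1 and section 6.2 all say double-blind. None of them limits the claim to subjects or to particular staff.

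2. **Are the codes masked?** No. Section 2 gives their meaning: control is the group without green tea and GT the group with it. A reader of the protocol needs no key to decode them.

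3. **Are the codes attached to individuals?** Yes. Section 10.1 combines them with subject numbers, so they are more than names for groups in a results table.

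4. **When do they apply?** Throughout the study, in the protocol's own terms. That covers baseline, week 6 and week 12, and does not begin only once the blind has been lifted.

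5. **Does another sentence shield the allocation?** The restriction in section 10.1 covers subject information and is justified by privacy. It says nothing about access to allocation. If anything, it leaves open that the one person who knows the subjects' identities also sees their arms.

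6. **Does another section supply a masked code?** No neutral code, kit number, key holder or time of unblinding appears in the protocol. This silence is not the defect, since such details may sit in operational documents. It means only that nothing in the protocol overrides the instruction in section 10.1.

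Steps 1 to 4 are enough: a stated labelling rule defeats a stated property of the design.

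**How exposed are the endpoints?** Section 6.1.1 names three primary endpoints: the Firmicutes/Bacteroidetes ratio, total faecal fat and body weight. Body weight is read from a digital balance (section 6.3.1). Faecal fat comes from a laboratory extraction (section 6.3.7). Observer judgement has little room in either. The remaining route to them is indirect: both can respond to diet, and faecal fat also to how complete the collection is, and staff give the instructions on both. The measures most directly open to the observer are secondary (section 6.1.2): waist circumference, waist-to-hip ratio, and resting energy expenditure with the respiratory quotient.

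**The case against.** The strongest reply is that section 10.1 is about privacy. The sentences around the quoted one deal with confidentiality, data protection law and linking results to the intervention rather than to persons. On that reading the sentence means only that numbers and group names replace personal names, and the masking arrangements may lie elsewhere. Section 5.1 refers to attachments and section 9.3 to a guideline on preparing and administering study products; neither is at hand.

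Part of this stands. The section does not say who sees the codes, and no section says who takes the measurements or who holds the allocation. Missing operational detail should not count as a separate defect.

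It does not remove the contradiction. Whatever its purpose, the sentence fixes an identifier that pairs a person with an arm, and its stated duration makes a reporting-only reading hard to sustain. The unseen documents cannot be assumed to overrule it. A statistical analysis plan would not normally repair a labelling rule for trial conduct that the protocol itself sets.

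A reader might infer more than the text supports, in four ways:

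- **That subjects are unblinded, so that their eating questionnaire answers are biased.** Nothing says that subjects see the codes.
- **That sample containers carry the code, so that the laboratory is unblinded.** Section 6.3.7 describes pre-weighed containers but no label.
- **That staff coach subjects by arm or treat incomplete collections differently by arm.** The protocol describes instructions to subjects and has no rule for incomplete collections, so this is conjecture.
- **That the trial cannot be reported as double-blind.** This follows only if the sentence is carried out literally and staff in contact with subjects use the coded records.

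**Conclusion.** The contradiction is certain on the text: section 10.1 cannot be followed as written alongside the double-blind claim in the Summary and sections 3.1 and 6.2. It must be reconciled before enrolment, because it concerns a core design property and the correction is cheap.

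The consequence is conditional. Assuming the sentence is followed literally, staff who work with records coded this way know the arm, and their blinding is not protected. This would apply to all subjects at all visits. The size of any resulting bias cannot be derived from the protocol, and no figure is offered. Exposure is greatest for tape-measured waist and hip, the conduct of the resting energy measurement, the instructions given to subjects, and decisions on withdrawal and replacement. It is lower for body weight and laboratory faecal fat.

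**What to change.** - **Section 10.1:** replace the four codes with the subject number, the BMI class (NW or Ob) and a neutral randomisation or capsule number that does not indicate the arm. Use this identifier on all working records and samples.
- **Section 6.2:** state that an existing staff member who takes no part in measurement or subject contact holds the key linking numbers to green tea or placebo. State that the key is opened only after database lock, or earlier for an individual subject if safety requires it.
- **Group names:** keep NW/control, Ob/control, NW/GT and Ob/GT for the analysis and for reporting after unblinding.

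The cost is small but not zero: a few sentences in two sections, relabelling before the first subject starts, one existing person's time to hold the key, and a defined unblinding step. The sample size, visits and measurements do not change.
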